### Sample size determination and power

The 6MP study aims to recruit 30 evaluable patients in the first stage, and 65 patients in total. The Simon compromise/admissible two-stage design [15, 16] was implemented to calculate this required sample size to detect an increase in response rate from 10% to 20%, with a power of 90% and a significance level of

20%. In the first stage of the study, if fewer than 3 out of 30 evaluable patients respond at 8 weeks after first treatment, then the trial will be stopped for futility; if 3 or more respond then a further 35 patients will be recruited in the second stage. If nine or more of the total 65 patients respond at 8 weeks then the treatment will be regarded as potentially effective and a phase III randomised trial will then be considered, if, in addition, the treatment appears to be safe and well tolerated, and the trial roll-out over multiple centres proves feasible.

### Statistical analysis

In the 6MP trial, fully evaluable patients (the per protocol population) are those patients who complete at least 4 out of 8 weeks of trial medication and are assessed for response as per RECIST v1.1 at 8 weeks. Patients who stop trial medication early due to disease progression (assessed by RECIST v1.1) are also fully evaluable because they have reached an end point. Partially evaluable patients (the intention to treat population) are those patients who have received at least one dose of treatment and who have a response assessment. Additional patients may be recruited at the discretion of the Chief Investigator to replace any that are not evaluable.

The proportion of patients responding to treatment will be presented, together with 95% confidence intervals, for Stage 1 (30 evaluable patients) and overall (65 evaluable patients). The number and proportion of patients who achieve CR, PR, SD and PD will also be reported, overall and separately for those patients who had received prior treatment with PARP inhibitors.

Overall survival and progression-free survival will both be presented overall and separately for patients previously treated with PARP inhibitors using Kaplan Meier graphs, and summarised as 1 and 2 year survival, together with their two-sided 95% confidence intervals. Median and quartile OS and PFS will also be presented. If the assumption of proportional hazards is met, the univariate hazard ratio (HR) from the Cox proportional hazards regression model will be given. In the case where the assumption of proportional hazards is inappropriate, parametric hazard functions will be considered.

Quality of life data will be presented descriptively overall and separately for patients previously treated with PARP inhibitors. Toxicity levels will be described using the NCI CTCAE version 4.0. Adverse Events (AEs) and Serious Adverse Events (SAEs) will be summarised by incidence rates and classified by the worst severity grade observed.

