### Interim analysis

A safety interim analysis was undertaken 3 months after the first 12 patients were recruited into the trial and had received at least one dose of the trial drugs. No issues with safety were found in this review, and any observed side effects were found to be as expected for this patient group. Another interim analysis was carried out 8 weeks after the first 30 patients were recruited (at the end of stage one), and again no safety concerns were raised and the events reported were found to be as expected. Also at this interim analysis stage, the first milestone was reached and passed, and a further 35 patients are now currently being recruited.

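### Both analysis sets require a response assessment, so treated patients who are never scanned drop out of the response rate and can be replaced; the set labelled intention to treat is not one

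*Protocol article*

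**What the plan says.** All references are to the protocol article.

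- **Statistical analysis, per protocol set.** The fully evaluable group is defined as "those patients who complete at least 4 out of 8 weeks of trial medication and are assessed for response as per RECIST v1.1", with the scan due at week 8. Early stops because of RECIST-assessed progression are also kept.
- **Statistical analysis, second set.** The wider group is described as "the intention to treat population) are those patients who have received at least one dose of treatment and who have a response assessment". There is no minimum time on drug and no stated scan time, but an assessment is still required.
- **Statistical analysis, replacement.** "Additional patients may be recruited at the discretion of the Chief Investigator to replace any that are not evaluable". No reason, number or limit is given.
- **Statistical analysis, primary estimate.** The response proportion is reported on 30 evaluable patients for stage 1 and 65 evaluable patients overall.
- **Sample size determination and power.** The trial "aims to recruit 30 evaluable patients in the first stage, and 65 patients in total", and is designed "to detect an increase in response rate from 10% to 20%, with a power of 90% and a significance level of" 20%. It stops if fewer than 3 of 30 evaluable patients respond, and the treatment is regarded as potentially effective if nine or more of 65 respond.
- **Outcomes and assessments.** Response is CR, PR or SD. Progressive disease is the only category named as non-response, so a treated patient with no assessment has no category.

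**The concern.** In a single-arm trial the denominator carries much of the inference. Whether a patient is assessed at 8 weeks is itself related to outcome: death, clinical decline or intolerance before the scan all prevent assessment. Dropping and replacing such patients removes likely failures and brings in new patients who may respond.

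The usual safeguard is an analysis of all treated patients beside the evaluable one. Here the set that carries that name applies the same condition of having an assessment, so it gives no protection against this loss.

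Replacement is also decided case by case, in an uncontrolled trial, by the Chief Investigator, who sits on the Internal Safety Monitoring Committee that reviewed the safety interims (Monitoring committees). At stake are the reported response rate and the error limit of the rule that opens the way to a phase III trial.

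**Working it through.** **1. Who is lost from which set**

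| Treated patient | Per protocol set | Set labelled intention to treat |
|---|---|---|
| Stops early, RECIST progression | kept | kept |
| Stops before 4 weeks for another reason, scanned | lost | kept |
| Dies, declines, stops or withdraws with no scan | lost | lost |

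The gap common to both sets is the last row. The per protocol set also loses the middle row.

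**2. The plan's own figure**

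Inputs from Sample size determination and power: stage 1 n = 30, continue at 3 or more; total N = 65, go at 9 or more; response rates 10% and 20%; power 90%; significance level 20%.

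P(go | p) = sum over x = 3 to 30 of P(X1 = x) × P(X2 ≥ 9 − x), with X1 ~ Bin(30, p) and X2 ~ Bin(35, p).

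- p = 0.10: P(go) = 0.183, within the 20% limit.
- p = 0.20: P(go) = 0.901, matching the stated 90%.

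The Abstract puts the final rule at more than 9 of 65. That gives 0.106 and 0.847 and does not reproduce the stated power, so nine or more is used below.

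**3. Effect of losing and replacing unscanned failures**

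Assumption: a share q of treated patients is unscanned, all of them are failures, and they are replaced until 30 and 65 are evaluable. The documents give no value for q. If the true rate in all treated patients is 10%, the rate among evaluable patients is 0.10/(1 − q). The number treated to reach 65 evaluable is 65/(1 − q), rounded up.

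| q | Evaluable rate | P(go) | Treated for 65 evaluable | 9 responses as share of treated |
|---|---|---|---|---|
| 0 | 10.0% | 0.183 | 65 | 13.8% |
| 5% | 10.5% | 0.224 | 69 | 13.0% |
| 10% | 11.1% | 0.272 | 73 | 12.3% |
| 15% | 11.8% | 0.330 | 77 | 11.7% |
| 20% | 12.5% | 0.398 | 82 | 11.0% |

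The 20% limit is passed at about q = 2.5% (P(go) = 0.202).

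**4. If the unscanned patients are not all failures**

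Let them respond at 5%. The evaluable rate is then (0.10 − 0.05q)/(1 − q).

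- q = 10%: 0.095/0.90 = 10.6%, P(go) = 0.226.
- q = 20%: 0.090/0.80 = 11.25%, P(go) = 0.284.

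If they respond at the same 10% as everyone else, the evaluable rate stays at 10% and there is no inflation.

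**5. Counting all dosed patients**

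With fixed cohorts of 30 and 65 dosed patients, and unassessed patients as non-responders, P(go) at an all-treated rate of 10% is again 0.183. If 20% was meant as the rate among evaluable patients, the all-treated rate is 0.20 × (1 − q):

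- q = 10%: 0.18, power 0.821.
- q = 15%: 0.17, power 0.765.

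**The case against.** **The plan keeps the main early failures.** RECIST-documented early progression stays in both sets, and a patient who stops before 4 weeks but is scanned stays in the second. This is right. A reader might infer that early failures in general leave the denominator, or that the two sets lose the same patients; the definitions do not support either. The point is confined to the patients in the last two rows of the first table.

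**Unscanned patients need not be failures, and there may be few.** Stable disease counts as response, so a patient who stopped for toxicity might have qualified. The dose cut described under Interventions might suggest that early toxicity stops are likely. That passage reports dose reductions and delays at the original starting doses, not discontinuations, and the Interim analysis section reports no safety concerns. The size is therefore unknown. The direction is upward only to the extent that excluded patients do worse than the rest.

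**The rule is stated for evaluable patients, and for them the error is still 0.183.** True, but a set conditioned on assessment does not describe the patients to whom the treatment would be given, and no all-treated figure is planned beside it.

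**Discretion covers recruiting replacements, not deciding who is evaluable.** Also true. Evaluability follows stated criteria, which limits the concern without removing it.

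**Stage 1.** The wording "Another interim analysis was carried out 8 weeks after the first 30 patients were recruited (at the end of stage one" invites the inference that stage 1 was judged on 30 recruited patients. It describes the timing of an interim look. The Abstract and the sample size section both refer to 30 evaluable patients, so the documents do not show that a wrong denominator was used.

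**It is a screening trial with a lenient error rate.** Passing only leads to a phase III trial being considered, subject to safety, tolerability and feasibility. This tempers the consequence; the stated 20% limit is still not protected.

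**Conclusion.** The concern holds in a limited form. Both sets exclude treated patients with no response assessment, those patients may be replaced without fixed criteria, and the intention-to-treat label is wrong. The per protocol set additionally loses patients who stop before 4 weeks for reasons other than RECIST progression.

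On the assumption that all excluded patients are failures and are replaced, the false-go probability at a true all-treated rate of 10% rises from 0.183 to 0.224, 0.272 or 0.398 at q = 5%, 10% or 20%. For a given q these are upper bounds, and q cannot be taken from the documents. A 5% response rate among those excluded brings the q = 10% figure down to 0.226, still above the 20% limit.

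**What to change.** 1. Base the primary proportion and both decision rules on all patients who received at least one dose, and count anyone without an 8-week response assessment as a non-responder.
2. Keep the evaluable set as a sensitivity analysis.
3. Rename the set now called intention to treat, since it requires an assessment.
4. Limit replacement to patients who were never dosed, or report every replaced patient with the reason.
5. State that 10% and 20% refer to all treated patients, or restate the power.
6. Align the Interim analysis wording with the sample size section: evaluable or dosed patients, and 8 weeks after first treatment. Nothing here calls for the stage 1 result to be re-stated on the ground that it used recruited patients.

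The cost is mainly wording. The reported rate will be somewhat lower. No patients beyond 65 dosed are needed if 20% is an all-treated target. If 20% was meant for evaluable patients, power with 65 dosed falls to about 0.82 at q = 10%, and the plan should say so.

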## Methods

### Study design

The 6MP study is a single arm, non-randomised, two-stage, multi-centre Phase II trial. The trial opened in June 2011 and recruits from 14 centres across the UK. Following written informed consent and screening tests, eligible patients will commence treatment, taking 6MP once daily and methotrexate once weekly. Treatment will continue until disease progression or unacceptable toxicity. Conduct of the 6MP trial complies with the ethical principles of the Declaration of Helsinki (1996) and the regulatory requirements for clinical trials of an investigational medicinal product under the European Union Clinical Trials Directive. The study has been approved by the National Research Ethics Service (NRES) Committee South Central – Oxford B (REC reference 10/H0605/79).

The trial is sponsored by the University of Oxford, with funding from Cancer Research UK’s Clinical Trials Award and Advisory Committee (CTAAC) who approved a full funding application on 26th October 2010, and this work was supported by the Oxford Partnership Comprehensive Biomedical Research Centre with funding from the Department of Health’s National Institute of Health Research (NIHR) Biomedical Research Centre funding scheme.

Data submission for the 6MP trial is via electronic submission into the online database system OpenClinica by site staff, and this is closely monitored. The Oncology Clinical Trial Office (OCTO) coordinates the trial, and OCTO staff are in charge of the day-to-day running of the trial, as well as managing the trial as a whole; organising trial meetings, completing trial documentation, site monitoring, and database management. All statistical analysis will be undertaken by statisticians at the Centre for Statistics in Medicine (CSM) at the University of Oxford.

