### Participants

To be eligible for inclusion in the 6MP study, patients must be aged 18 or older, have proven BRCA1 or BRCA2 mutations, and have measurable disease as defined by RECIST v1.1 criteria. For breast cancer patients, patients must have locally advanced or metastatic breast cancer, and may have received up to 3 previous lines of chemotherapy in the locally advanced or metastatic setting. Ovarian, fallopian tube or primary serous peritoneal cancer patients must have disease that is either platinum resistant or in whom further platinum based therapy is inappropriate. All patients must have an Eastern Cooperative Oncology Group (ECOG) performance score between 0 and 2, a life expectancy of greater than 12 weeks, and adequate haematological and biochemical function. Patients are excluded from participating in the study if they have a Low/Low genotype on Thiopurine methyltransferase (TPMT) testing. Patients with low activity (10% prevalence) or especially absent activity (prevalence 0.3%) are at a heightened risk of drug-induced bone marrow toxicity due to accumulation of the unmetabolised 6MP. At the start of the trial, patients were excluded from participation if they had low TPMT activity (<68 U/ml), but a decision was made by the 6MP TMG in October 2013 to remove this exclusion as a substantial amendment to the protocol, as evidence suggested that moderate TPMT activity levels did not affect dose intensity or levels of myelosuppression seen. Patients were already being closely monitored in the first cycle therefore no additional monitoring was implemented for this patient group. A total of 14 sites across the UK are actively recruiting for this trial; Royal United Hospital, Bath; Belfast City Hospital, Belfast; Velindre Hospital, Cardiff; University Hospital, Coventry and Warwickshire; Western General Hospital, Edinburgh; Guy’s Hospital, London; Royal Marsden Hospital, London; University College London Hospital, London; Christie Hospital, Manchester; Freeman Hospital, Newcastle; Mount Vernon Hospital, Middlesex; Churchill Hospital, Oxford; Royal Marsden Hospital, Sutton; Clatterbridge, Wirral.

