### Outcomes and assessments

The primary outcome of the 6MP study is objective response, defined as complete response (CR), partial response (PR), or stable disease (SD), as measured by radiological disease response using RECIST criteria version 1.1. Patients who yield progressive disease (PD) are classed as non-responders. Tumour size is measured radiologically with computerised tomography (CT) and/or magnetic resonance imaging (MRI); the same method is used at baseline and at follow-up. The first time point for this primary analysis is 8 weeks after first treatment.

Secondary outcome measures include safety, overall survival (OS) and progression-free survival (PFS). Length of overall survival is defined in whole days as the time from entry into the study until death from any cause, and those patients who are not observed to die during the course of the trial will be censored at their last known follow-up date. Length of progression-free survival is defined in whole days as the time from entry into the study until progression or death from any cause, and those patients who are not observed to progress or die during the course of the trial will be censored at their last known progression- free follow-up date. Grade 3 or 4 Adverse Events (AEs), as defined by the National Cancer Institute (NCI) Common Terminology Criteria for Adverse Events (CTCAE) version 4.0, and abnormal clinical and laboratory findings will be collected at regular follow-up visits throughout the trial in order to evaluate safety. Pharmacokinetics are measured by the assessment of red blood cell 6-thioguanine nucleotide (6TGN) levels using a validated high-performance liquid chromatography (HPLC) assay, and the effect of pharmacogenomics on thiopurine metabolism is measured by assessing the TPMT genotype using a validated assay. Another secondary outcome is quality of life, which is evaluated using the EQ-5D questionnaire at baseline, 3 and 6 months, and at the end of treatment or 12 months, as well as using the ECOG performance status measure after each cycle.

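### The univariate Cox hazard ratio has no stated contrast, its likely one (prior PARP inhibitor or not) is non-randomised, and the parametric fallback need not address non-proportional hazards

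*Protocol article*

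**What the plan says.** The Study design section of the protocol article describes a "single arm, non-randomised, two-stage, multi-centre Phase II trial". There is therefore no concurrent control group.

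The Statistical analysis section sets out the survival analyses in one paragraph:

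- Presentation: "Overall survival and progression-free survival will both be presented overall and separately for patients previously treated with PARP inhibitors using Kaplan Meier graphs". One- and two-year survival with two-sided 95% confidence intervals, medians and quartiles are added.
- Hazard ratio: "If the assumption of proportional hazards is met, the univariate hazard ratio (HR) from the Cox proportional hazards regression model will be given".
- Fallback: "In the case where the assumption of proportional hazards is inappropriate, parametric hazard functions will be considered".

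The HR sentence names no covariate and no reference group. The fallback sentence names no parametric family. Overall and progression-free survival are secondary outcomes (Outcomes and assessments). The rule for moving to phase III uses response at 8 weeks, safety, tolerability and feasibility (Sample size determination and power). The HR plays no part in it.

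**The concern.** An HR compares two groups, and this trial has one arm. The reader must infer the comparison, and prior PARP inhibitor treatment is the only grouping in the paragraph. If that is what is meant, a univariate model compares patients who differ in more than PARP exposure. The Participants section admits two kinds of disease under different conditions. A breast cancer patient "may have received up to 3 previous lines of chemotherapy in the locally advanced or metastatic setting", while ovarian, tubal and peritoneal patients must be platinum resistant or no longer suitable for platinum. Nothing in the design balances prior PARP treatment across these groups.

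The fallback raises a separate question. Whether the baseline hazard has a parametric shape is one matter, and whether the hazards in two groups are proportional is another. Giving the baseline a parametric form does not relax proportionality.

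Activity after PARP inhibitor resistance is the trial's motivating question (Abstract, Discussion). Readers are likely to look at this HR, and it could reflect tumour mix or average over an effect that changes with time.

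**Working it through.** The article gives no figure for the HR analysis: no event count, no target HR and no share of PARP-pretreated patients. There is nothing to reproduce, and every input below except the total of 65 patients is an assumption for illustration.

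**1. Confounding by tumour type**

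Assumptions: prior PARP treatment has no effect; it was given to 50% of ovarian and 10% of breast patients; survival is exponential; there is no censoring.

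With 70% ovarian patients, the exposed share is 0.7 × 0.5 + 0.3 × 0.1 = 0.38. The exposed group is 0.35/0.38 = 92% ovarian and the unexposed group 0.35/0.62 = 56% ovarian.

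In large samples the univariate Cox log HR is the β that solves

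∫ [e₁(t) − (e₁(t) + e₀(t)) · R₁(t)e^β / (R₁(t)e^β + R₀(t))] dt = 0,

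where R₁ and R₀ are the proportions of all patients who are exposed or unexposed and still at risk at time t, and e₁ and e₀ are the matching event densities, each summed over the two tumour types. The true HR is 1.0, and a Cox model stratified by tumour type recovers about 1.0.

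| Ovarian share | Breast hazard relative to ovarian | Univariate HR |
|---|---|---|
| 70% | 1.5 | 0.88 |
| 70% | 2 | 0.82 |
| 70% | 3 | 0.77 |
| 50% | 1.5 | 0.84 |
| 50% | 2 | 0.76 |
| 50% | 3 | 0.68 |
| 70% | 1/1.5 (ovarian higher) | 1.16 |
| 50% | 1/2 (ovarian higher) | 1.37 |

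The distortion can go either way, depending on which tumour type has the higher hazard and on how PARP exposure is spread. The article gives neither.

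**2. Precision**

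Assume 20 of 65 patients exposed and 60 events.

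SE(log HR) = √[1/(60 × 0.308 × 0.692)] = 0.280, and exp(1.96 × 0.280) = 1.73.

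The 95% confidence interval is the HR divided and multiplied by 1.73. An HR of 0.82 has an interval of about 0.47 to 1.42. With 40 to 65 events and 10% to 50% exposed, the factor runs from about 1.6 to 2.8.

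**3. The fallback**

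Take two groups with Weibull survival, shapes 1.5 and 0.7, equal medians set to 1, and follow-up ending at t = 3. The true HR at time t is (1.5/0.7) × t^0.8, which is 0.34 at t = 0.1, 2.14 at t = 1 and 5.16 at t = 3. Fits to 6,000 simulated patients give:

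| Model | Result |
|---|---|
| Cox | constant HR 1.61 |
| Exponential | constant HR 1.59 |
| Weibull, common shape | constant HR 1.58, log-likelihood −7053 |
| Weibull, separate shapes | shapes 0.68 and 1.46, log-likelihood −6524 |

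The exponential and common-shape Weibull models return nearly the same single number as Cox. A Gompertz regression with a common shape also imposes a constant ratio. Only the form that lets the shape differ between groups captures the crossing.

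**4. Letting a check decide what is reported**

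The article names no test of proportional hazards. As an illustration, take 20 versus 45 patients, all with events, and tests of trend in the log HR against ranked time at the 5% level. Depending on the version of the test, Weibull shapes of 1.3 and 0.9 are detected in about 23% to 36% of trials, and shapes of 1.5 and 0.7 in about 75% to 89%. At this size, moderate non-proportionality would often pass unnoticed.

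**The case against.** The strongest reply has four parts.

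- **The contrast is inferred.** A reader might conclude that the plan produces a confounded PARP effect. The article does not say that the HR compares patients with and without prior PARP inhibitors, and it does not report PARP exposure by tumour type. Confounding is a possibility, and its size and direction come from assumed inputs. This stands.
- **The fallback is left open.** A reader might conclude that the fallback is wrong in itself. The text only says that parametric functions will be considered. Log-logistic, log-normal or separate-shape Weibull models do not impose proportional hazards, and the wording permits them. This also stands. What can be said is that the stated remedy does not by itself address the failure it is written for.
- **Little depends on the HR.** It is secondary, openly univariate, and carries no test, threshold or causal claim. Response categories and Kaplan-Meier summaries for PARP-pretreated patients are planned in any case. Under the central assumptions the distortion to 0.82 lies well within the interval of 0.47 to 1.42. This limits the severity.
- **Such detail belongs in an analysis plan.** Covariates and model families are often fixed there, and that document is not shown. This holds for the detail. It does not fully answer the point, because the article itself states an unadjusted HR and a parametric remedy for non-proportionality.

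A further fair remark is that an unadjusted Kaplan-Meier or restricted-mean difference carries the same confounding as the univariate HR. The fix has to allow for that.

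**Conclusion.** The point holds as a minor one. The article states a univariate HR in a single-arm trial without naming what is compared. The likely contrast is non-randomised and open to confounding by tumour type, and the parametric fallback need not deal with non-proportional hazards.

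The illustrated size is a univariate HR between 0.68 and 1.37 when the truth is 1.0. It rests on the assumed PARP exposure of 50% and 10%, an ovarian share of 50% to 70%, breast hazards of 1.5 to 3 times ovarian or ovarian hazards of 1.5 to 2 times breast, and exponential survival without censoring.

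It would be tempting to infer that the trial's main conclusion is at risk. The article does not support that, because the decision rule uses response at 8 weeks, safety, tolerability and feasibility, and none of these depends on the HR.

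**What to change.** In the Statistical analysis section, or in the analysis plan if it is still open:

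1. Name the contrast: prior PARP inhibitor versus none.
2. Beside the univariate HR, report the HR from a Cox model stratified by tumour type (breast versus ovarian, tubal or peritoneal). Label both as descriptive.
3. Replace the parametric fallback with the between-group difference in the planned 1- and 2-year Kaplan-Meier rates, or in restricted mean survival time to a fixed horizon, with a 95% confidence interval. Report it whatever the proportional-hazards check shows.
4. Give that difference by tumour type as well where numbers allow, since the unadjusted difference is confounded in the same way as the univariate HR.

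The cost is slightly wider intervals from stratification and a little more analysis. Tumour type is already known from eligibility, so no new data are needed, and the primary response rule is unchanged.
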